## IV. The overall design of the trial

**1. Sample size**

The sample size of the trial is designed and estimated according to non-inferiority test. The assumption of non-inferiority test is that the Xiaoke pill is not inferior to glibenclamide in terms of reducing HbA1c. Xiaoke Pill was regarded as non-inferior to treatment with Glibenclamide only if, after 48 weeks of treatment, the upper limit of the two-sided 95% CI for the difference in mean HbA1c change was less than 0.4%. A sample size of 400 patients was estimated to provide more than 90% power to test the hypothesis that Xiaoke Pill treatment was non-inferior to treatment with Glibenclamide in each of the study groups, assuming a 20% early discontinuation rate, and an expected inter-patient SD of 1.1%. The sample size estimation is based on being able to provide sufficient amount of information.

According to statistical results of sample size, in order to better guide the clinical application of Xiaoke Pills to improve the effectiveness of medication, this study is plan to enroll 400 non-obese patients with type 2 diabetes who have not received any antidiabetic agents before and have unsatisfactory glycemic control on diet and exercise and 400 patients with type 2 diabetes who have unsatisfactory glycemic control after treatment with metformin alone for over 3 months. 800 patients will be randomly assigned to the treatment groups and control group.

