**2. Trial goals**

2.1 To discover biomarkers related to the clinical efficacy of Xiaoke Pills with glibenclamide as a reference.

2.2 To discover biomarkers related to the main side effect, i.e., hypoglycemia and study pathophysiological and clinical features of susceptibility to hypoglycemia.

2.3 To discover the unique efficacy of Xiaoke Pills compared with sulfonylureas, as well as the biomarkers associated with the unique efficacy of Xiaoke Pills.

2.4 To discover biomarkers, pathophysiological and clinical features associated with secondary failure of sulfonylureas. To investigate if Xiaoke Pills can reduce the risk of secondary failure of sulfonylureas as compared with glibenclamide.

2.5 Apply the TCM evaluation indexes to evaluate the efficacy and safety of Xiaoke Pills and glibenclamide tablets from the view of treatment of type 2 diabetes belonging to the syndrome of dual deficiency of qi and yin, and to found the biomarkers associated with above evaluation indexes.

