## VI. Dosage regimens

**1. Study drugs**

**Investigational drug**: Xiaoke Pills (each pill contains glibenclamide 0.25mg + Chinese herbs), produced by Guangzhou Zhongyi Pharmaceutical Co, Approval Document Number: SFDA (approved) Z44020045, production batch number: K03300, shelf life: 3 years.

**Control drug:** glibenclamide tablets, 2.5 mg/tablet, produced by Tianjin Pacific Pharmaceutical Co., Ltd., Approval Document Number: SFDA (approved) H12020790, production batch number: 070708, shelf life: 3 years.

**Simulators:** The simulator of Xiaoke Pills and simulator of glibenclamide tablets are prepared in line with the requirements for placebo preparation, which are pills or tablets not containing any active ingredient.

**Basic medication** (patients treated with metformin): metformin hydrochloride tablets, 0.25 g/tablet, purchased by the Guangzhou Zhongyi Pharmaceutical Co., Ltd., Approval Document Number: SFDA (approved) H11020976, shelf life: 3 years.

In order to ensure the implementation of the blindmethod, the study drugs of the trial will be divided into No.1 medication and No.2 medication. No.1 medication includes Xiaoke Pills and simulator of Xiaoke Pills, while No.2 medication includes glibenclamide tablets and simulator of glibenclamide tablets.

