## XII. Statistical analysis

**1. General considerations**

The efficacy analysis will be based on intention to treat (ITT) population, with supportive analysis with per protocol set (PPS). The PPS includes all randomized patients who have received treatment with study drugs for 48 weeks without violation to inclusion/exclusion criteria or criteria for termination of the study. The ITT population includes all randomized patients receiving at least one dose of study drugs. The safety analysis will be based on ITT population.

For efficacy analyses, changes in the primary and secondary study parameters at 48 week from baseline will be measured, and the inference on the possible non-inferiority will be based on the upper limit of the 95% confidence intervals of the difference in mean changes at 48 week. The incidence and average rate of hypoglycemia will be analyzed using appropriate statistical methods.

A separate statistical analysis plan will be developed in due course detailing all aspects of data analysis. Appropriate exploratory analyses will be conducted, as deemed appropriate.

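### The only stated efficacy inference is non-inferiority to glibenclamide, which both arms receive at planned matched doses, so meeting it says nothing about what the herbs add and leaves goals 2.3 and 2.4 largely without a test

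*Protocol*

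**What the plan says.** **Decision rule.** Protocol IV.1 states that "The sample size of the trial is designed and estimated according to non-inferiority test". Success means that, after 48 weeks, "the upper limit of the two-sided 95% CI for the difference in mean HbA1c change was less than 0.4" (in % HbA1c). XII.1 covers changes in both primary and secondary parameters, and says that "the inference on the possible non-inferiority will be based on the upper limit of the 95% confidence intervals" of the difference in mean change. A margin is given only for HbA1c. No superiority hypothesis is stated.

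**What the arms receive.** VI.1 describes the test product thus: "each pill contains glibenclamide 0.25mg + Chinese herbs". The control tablet holds 2.5 mg. Under VI.4 both arms run from 5 pills or half a tablet to 30 pills or 3 tablets a day. Under VI.5 they move by 5 pills or half a tablet on one fasting-glucose rule.

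**What the trial sets out to learn.** Goal 2.3 in section II.2 is "To discover the unique efficacy of Xiaoke Pills compared with sulfonylureas", with its biomarkers. Goal 2.4 includes "To investigate if Xiaoke Pills can reduce the risk of secondary failure of sulfonylureas as compared with glibenclamide". The background (section I) regards a glucose-lowering effect of traditional Chinese medicine in humans as unsettled. The anticipated-results section expects similar glycaemic control in the two arms.

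**The concern.** When test and comparator share the same active drug at the same planned dose, non-inferiority is the result to expect whether the herbs help or do nothing. The rule excludes a harm of 0.4% HbA1c or more, which is useful, but it cannot separate useful herbs from inert ones.

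Goals 2.3 and 2.4 are directional: does the compound do something that the sulfonylurea alone does not, and does it lower the risk of failure? A non-inferiority conclusion on HbA1c answers neither. Secondary failure is also not defined and is absent from the endpoints in section III. The trial could therefore meet its stated criterion and leave unanswered the question that the herbs raise, although the randomised data could address it.

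**Working it through.** **Step 1. Planned glibenclamide by dose level** (0.25 mg per pill, 2.5 mg per tablet, dose levels from VI.5)

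| Pills | Tablets printed | mg from pills | mg from tablets |
|---|---|---|---|
| 5 | 0.5 | 1.25 | 1.25 |
| 10 | 1.5, then 1 | 2.5 | 3.75 or 2.5 |
| 15 | 1.5 | 3.75 | 3.75 |
| 20 | 2 | 5.0 | 5.0 |
| 25 | 2.5 | 6.25 | 6.25 |
| 30 | 3 | 7.5 | 7.5 |

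Five of the six levels match, as does the paired 1.25 mg step. The second item under medication times prints two different tablet counts against 10 pills. That line contradicts itself and must be reconciled.

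**Step 2. Reproduce the stated size.** Inputs from IV.1: margin 0.4, two-sided 95% interval (one-sided 0.025), and the statement that "A sample size of 400 patients was estimated to provide more than 90% power" "in each of the study groups, assuming a 20% early discontinuation rate, and an expected inter-patient SD of 1.1" (%). The true difference is not stated and is taken as 0.

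- n per arm = 2 × (1.96 + 1.282)² × 1.1² / 0.4² = 159, so 318 in total.
- Allowing for discontinuation: 318 / (1 − 0.20) = 398, against 400 stated.

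The figure reproduces for one cohort of 400 (200:200 in the IV.6 allocation table), which leaves 160 per arm after 20% loss.

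**Step 3. Chance that the rule is met when the herbs do nothing.** P = Φ(0.4/SE − 1.96), with SE = 1.1 × √(2/n).

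- Per cohort, n = 160: SE = 0.123 and P = Φ(3.25 − 1.96) = 0.902 (noncentral t: 0.900).
- Cohorts pooled, n = 320: SE = 0.087 and P = 0.996. The protocol states no pooled rule, so this is illustrative only.

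**Step 4. If the herbs worsen HbA1c by d.** P = Φ((0.4 − d)/SE − 1.96).

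| d (% HbA1c) | Per cohort | If pooled |
|---|---|---|
| 0.1 | 0.684 | 0.932 |
| 0.2 | 0.369 | 0.633 |

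**Step 5. Superiority on the same interval (upper limit below 0).**

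- Inert herbs pass 2.5% of the time.
- True benefit detectable with 80% power = (1.96 + 0.842) × SE = 0.345% per cohort, or 0.244% if pooled.
- At a true benefit of 0.3%, power is 0.684 per cohort, or 0.932 if pooled.

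These figures take the SD of 1.1% as given and make no allowance for the effect of titration on the size of the difference.

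**The case against.** **The 90% is ordinary power.** This stands. At a true difference of 0, non-inferiority is the correct conclusion. A reader might infer that 90% to 99.6% is a false-positive rate, but it is not. The upper figure also needs pooling, whereas IV.1 powers each cohort.

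**Goal 2.4 is not wholly untested.** This stands in part. XII.2 compares reasons for termination between arms by Fisher's exact test, and section V.5 lists lack of efficacy among those reasons. Section VIII also counts patients reaching the endpoint at 3, 6 and 9 months. So the reading that the protocol has no between-arm test bearing on failure is unsupported. It remains a disposition analysis, not tied to a defined secondary-failure outcome.

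**The herbs are not strictly the only difference.** This also stands. Doses are titrated individually, so realised exposure can diverge. The package inserts give different times to peak concentration (2–3 hours for the pill, 2–5 for the tablet). The 10-pill line bars the claim that the printed doses agree at every step. What the text supports is planned matching.

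**HbA1c superiority may miss a real herb effect.** Both arms are titrated to the same fasting-glucose band, so a benefit could appear as a lower glibenclamide dose. This limits the added test, and it also makes a finding of similar HbA1c less informative.

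**The SAP may supply the tests.** XII.1 defers analysis detail to it. But the hypothesis, the decision rule and the goals are all fixed in the protocol, and they do not match one another there.

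**Goal 2.3 is a discovery goal.** Fair, and section III.2 lists outcomes where unique effects could be sought. That argues for exploratory labels, not for a non-inferiority inference on those outcomes.

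**Conclusion.** The point holds as a mismatch between the stated goals and the stated inference. It does not show that the design is invalid or the sample size wrong. The size reproduces, and non-inferiority is a legitimate first question.

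With inert herbs the rule is met about 90% of the time per cohort, so meeting it carries no evidence of a herb effect on glucose. It supports only the statement that adding the herbs does not worsen HbA1c by 0.4% or more. Goal 2.3 has no matching inference, and goal 2.4 has only the XII.2 comparison. A reader might go further and say that the trial cannot answer these goals. The documents do not support that, because the limit lies in the rule and not in the randomised data.

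The figures assume SD 1.1%, 20% discontinuation, 160 per arm per cohort and a true difference of 0 where stated. The reading as an add-on comparison rests on planned, not realised, dose matching.

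**What to change.** 1. In IV.1 and XII.1, add a fixed-sequence step: if non-inferiority is shown in a cohort, test superiority on the same 95% interval (upper limit below 0) at the same alpha. Within a cohort this costs no alpha. Quote the detectable benefit: about 0.35% HbA1c with 80% power per cohort (0.24% only if a pooled analysis is specified).
2. Name the endpoints that serve goals 2.3 and 2.4, including which recorded outcome represents secondary failure. Analyse them by between-arm difference tests labelled secondary or exploratory, since the alpha-free property covers only the HbA1c step.
3. State that non-inferiority alone supports only that adding the herbs does not worsen HbA1c by 0.4% or more.
4. Report final glibenclamide dose by arm beside the HbA1c result, and note that common titration may shrink the difference.
5. Reconcile the 10-pill line in VI.5.

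The cost is a few sentences, with no additional patients or visits. The superiority step should be written in before unblinding.

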**2. Design of the trial**

This study is a randomized, double blind and double dummy, masculine parallel comparison, multi-center clinical trial.

It is estimated that a total of 1600 type 2 diabetes patients with unsatisfactory glycemic control will participate in preliminary screening, of which 800 patients have not used any hypoglycemic agents and are non-obese (hereinafter referred to patients for initial treatment), and 800 patients have unsatisfactory glycemic control after treatment with metformin alone for over 3 months (hereinafter referred to patients treated with metformin). After determined as eligible through preliminary screening, about 1,000 patients (each 500 of patients for initial treatment and patients treated with metformin) will enter the four-week run-in period. During the run-in period, it will maintain the same normal dose of metformin for patients treated with metformin, in addition to diet and exercise management.

After the end of run-in, those who still meet the inclusion criteria (a total of 800 patients, including each 400 in the initial treatment group and metformin treatment group) will be randomly divided into the test group and control group, i.e., Xiaoke Pills group and glibenclamide group (n = 400 patients). In the glibenclamide group, the initial dose is glibenclamide 1.25 mg (0.5 tablets) with simulator of Xiaoke Pills 5 pills, once daily, and the maximal dose is glibenclamide 7.5 mg/d for oral administration in 3 times; in the Xiaoke Pills group, the initial dose is Xiaoke Pills 5 pills with simulator of glibenclamide tablets 1.25 mg (0.5 tablets), once daily, and the maximal dose is Xiaoke Pills 30 pills/d for oral administration in 3 times. Each subject will be followed up for 48 weeks, and the necessity for dose adjustment will be evaluated every 4 weeks according to fasting blood glucose levels. If the patient has achieved the Study Termination Criteria of the clinical trial, then the trial is terminated and transferred to conventional treatment, while the treatment methods comply with the “China Guidelines for Diabetes Prevention and Treatment”.

**3. Trial procedures**

4 weeks

Control group (glibenclamide)

Run-in period

Test group (Xiaoke pills)

组

48 weeks

Initially treated patients

/Metformin treated patients

Randomization

**4. Randomization**

Biometric experts will use SAS software to randomly divide the subjects who have been determined as eligible through screening in the run-in period into group A or group B, after stratification according to initial treatment and metformin treatment as well as test centers. The specific method of randomization is:

1. Each case to be observed will be given a code like 001-800;
2. Biometric experts will use the SAS statistical software procedure statement of the computer to assign the number of seeds and number of centers, automatically obtaining the random number table; through the random number table, the random number is obtained, which is one-to-one with the case code;
3. Patients are divided into group A and group B according to the ratio of 1:1, and treatment of the two groups will be randomly decided;
4. Corresponding kit is prepared according to the case code and grouping, and the medication number is as the same as the case code;

⑤ When eligible patients enter the test, according to the order of entry, find the kit of the same number as the case code to give treatment.

The treatment of enrolled subjects is only known by the data centers and drug distribution centers, while both the subjects and investigators do not know the situation on grouping.

**5. Preservation of blind codes and regulation on unblinding**

5.1 Preservation of blind codes:

The two-level blind method is adopted for design, the first level is that the corresponding group of each case code is either group A or group B, and the second level is that the corresponding treatment of the two groups is either the test group or control group. The blind codes of the two levels is sealed separately, each in duplicate, which are respectively preserved in the drug clinical trial test base of the team leader’s unit and the sponsor.

5.2 Emergency unblinding:

Each study drug with a code has a corresponding emergency letter, and a paper strip recorded with the type of treatment given to the drug of the code is placed in the emergency letter, so as to be used for unblinding in case of emergency. In case of emergency or serious adverse events when the subjects require emergent rescue, the principal investigator of the center determine whether it needs to open the emergency letter. Once the emergency letter is opened, the case is considered as lost, which will not be included in efficacy analysis, but if there are any adverse reactions, it should be included in the analysis of adverse reactions.

5.3 Regulation on unblinding:

Two times of unblinding is used in this trial. After completion of data entry and inspection of blinded state, the data is locked. The first unblinding is performed by the personnel of Statistics Centre who keeps the blind end, i.e., inform the corresponding group of each case code to biostatistician using the code name A or B for statistical analysis of all data. When the statistical analysis is ended and the statistical report is completed, the second unblinding is performed by the sponsor and the team leader’s unit to announce the treatment of group A and B, and finally complete the clinical trial summary report.

In the process of the clinical trial, if all the blind ends are disclosed or over 20% of the emergency letters are opened and read, this double-blind trail is failed.

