**4. Loss criteria**

4.1 Definition: All subjects who have completed the informed consent, been determined as eligible through screening in the run-in period and have been randomized into the trial, are considered as loss cases as long as if they do not complete the observational period specified in the protocol, no matter at any time and due to any reason.

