**5. Termination (withdrawal)**

In the following situations, the study will be terminated for the patients, but the patients will be included in the FAS statistics:

5.1 If the female patient gets pregnant (violation to the protocol).

5.2 If the patient has not used the study drugs (including metformin) in accordance with therequirements of the protocol for more than 7 consecutive days.

5.3 If the patient has used insulin for more than 7 days, or month than 7 days within 1 month.

5.4 If the patient has used combined therapy with the drugs that should be excluded for more than 7 days.

5.5 If the patient’s (finger whole blood) fasting blood glucose has been greater than 234 mg/dL (13 mmol/L) for 3 consecutive times (lack of efficacy).

5.6 Serious adverse events occur.

5.7 If the patient has recurrent hypoglycemia (more than 2 episodes of hypoglycemia per week in 4 consecutive weeks), especially severe hypoglycemia (more than 2 episodes of severe hypoglycemia within 30 days), the investigator must consider terminating the trial for the patient.

If the investigators determine the patients should withdraw from the trail because of serious adverse events or significantly increased clinical laboratory parameters, appropriate measures should be taken immediately and the principal of the study should be notified.

The investigators terminate the trial or terminate the patients to participate in the trial for any reason; those patients under early termination will continue to carry out the visit procedures for early termination as specified in the protocol procedures.

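### The emergency-unblinding rule removes from the efficacy analysis patients whom the ITT definition keeps, and the trigger is a safety event after randomisation

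*Protocol*

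**What the plan says.** Four places in the protocol bear on the same patient.

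- **IV.5.2, Emergency unblinding.** The letter may be opened "In case of emergency or serious adverse events when the subjects require emergent rescue", and the centre's principal investigator decides. The consequence is: "Once the emergency letter is opened, the case is considered as lost, which will not be included in efficacy analysis". Such a patient is kept only for the analysis of adverse reactions.
- **XII.1, General considerations.** "The efficacy analysis will be based on intention to treat (ITT) population", and "The ITT population includes all randomized patients receiving at least one dose of study drugs". Nothing is said about broken codes, here or in the PPS definition.
- **V.5, Termination (withdrawal).** For the listed reasons, "the study will be terminated for the patients, but the patients will be included in the FAS statistics". Item 5.6 on that list reads "Serious adverse events occur".
- **V.4, Loss criteria.** Randomised patients "are considered as loss cases as long as if they do not complete the observational period specified in the protocol". This defines a loss case but does not remove it from the efficacy analysis.

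IV.5.3 adds that if "over 20% of the emergency letters are opened and read, this double-blind trail is failed".

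**The concern.** The protocol defers analysis detail to a separate SAP, but it already fixes both rules itself. A SAP that follows one must depart from the other, so the conflict has to be settled in the protocol.

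If IV.5.2 prevails, the population called ITT loses dosed patients because of something that happened after randomisation. Both arms contain glibenclamide. The protocol's table of hypoglycaemic reactions says severe hypoglycaemia needs emergency treatment, so it is a plausible reason to open a letter. It may be related to treatment and to glycaemic control. If the arms differ in how many patients are removed, or in what kind, the HbA1c comparison is no longer the randomised one.

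A second effect concerns hypoglycaemia. Its incidence and rate is secondary endpoint 2.1, yet IV.5.2 keeps these patients for adverse reactions only. Whether their episodes count towards that endpoint is unclear.

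**Working it through.** **1. One patient under the rules.** Take a randomised, dosed patient with a serious adverse event.

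| Rule | Letter stays sealed | Letter opened |
|---|---|---|
| XII.1 (ITT) | in efficacy | in efficacy |
| V.5, item 5.6 (FAS) | in | in |
| IV.5.2 | not affected | out of efficacy |

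The direct conflict is between IV.5.2 and XII.1. V.5 supports it only if FAS means the same set as ITT, which the protocol does not say. V.4 does not resolve it: a loss case there is a non-completer, and opening a letter is not in itself non-completion.

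**2. The plan's own figure.** Inputs from IV.1: margin 0.4, SD 1.1, two-sided 95% CI, power above 90%, 20% discontinuation, 400 patients per stratum. Allocation is 1:1 (IV.4). A true difference of 0 is assumed.

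- n per arm = 2 × (1.960 + 1.282)² × 1.1² / 0.4² = 159, so 318 per stratum.
- 318 / 0.80 = 398, against 400 stated.
- Power on 320 completers is 0.902, against more than 90% stated.

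The design figure reproduces, and the point does not touch it.

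**3. Shift in the arm difference.** Let p be the share removed in an arm and D the amount by which the removed patients' mean HbA1c change differs from that of the patients who remain. The full-arm mean is the retained mean plus p × D, so

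full difference − retained difference = p₁D₁ − p₂D₂.

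All rates and deviations below are assumptions; the protocol gives none.

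- 6% v 2%, D = 1.0 in both arms: (0.06 − 0.02) × 1.0 = 0.04, and 0.04 / 0.4 is a tenth of the margin. In a stratum of 200 per arm this is 12 v 4 patients.
- 5% v 2%, with the deviation measured from the whole arm's mean, so that each arm shifts by pD/(1 − p): (0.05/0.95 − 0.02/0.98) × D = 0.0322 × D. This is 0.016 for D = 0.5 and 0.048 for D = 1.5.
- 5% v 5%, same D in both arms: 0.

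The sign is open. With the difference taken as Xiaoke minus glibenclamide, a positive p₁D₁ − p₂D₂ (arm 1 being Xiaoke) means that deletion flatters Xiaoke; a negative value means the reverse.

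**4. Power.** Take each stratum of 400 with 20% discontinuation. If no opened-letter patient is among the discontinuations (the worst case), power is 0.898 with 1% opened, 0.895 with 2% and 0.883 with 5%. If all of them are already among the discontinuations, power stays at 0.902.

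**5. The 20% limit.** 20% × 800 = 160 letters. IV.5.3 uses this as the point beyond which the double blind is declared failed.

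**The case against.** The strongest reply is that the practical effect is likely to be small. Much of that stands.

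- **Matched doses.** Each pill contains 0.25 mg glibenclamide, so 5 × 0.25 = 1.25 mg, the same as half a tablet. A large difference between arms in severe hypoglycaemia is not the natural assumption. The one earlier trial the protocol cites with hypoglycaemia counts had three mild events among 450 subjects. That is weak evidence, because the protocol itself calls those trials poor and they lasted only 4 to 8 weeks.
- **Overlap with discontinuation.** A serious adverse event is itself a termination reason, so many opened-letter patients would lack an on-treatment week-48 HbA1c under any rule. The shift formula treats them as contributing a complete outcome. The real effect therefore also depends on how missing values are handled.

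The documents do not support four stronger readings that a reader might infer.

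- *That patients are dropped because of the outcome.* The trigger is an emergency or serious adverse event, not the HbA1c result. It can be an episode belonging to the hypoglycaemia endpoint, but it is not the primary outcome.
- *That the exclusion protects no blinded endpoint.* Central-laboratory measurement supports this for HbA1c only. Efficacy also includes the TCM syndrome, scored from symptoms, and hypoglycaemia can be counted on what the patient feels. That justifies a sensitivity analysis, not deletion from ITT.
- *That the result turns on how readily each centre opens letters.* Randomisation is 1:1 and stratified by centre, and the investigator decides while still blinded. Readiness alone acts on both arms alike; bias needs different event rates or different kinds of patient removed.
- *That up to 160 patients are expected to go, or that the shift may reach a quarter of the margin.* The 160 is a failure ceiling, not a forecast. Removals of 20% v 10% with D = 1.0 would give 0.10, but nothing in the protocol supports such rates or such an imbalance.

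One could also read IV.5.2 as a specific exception to XII.1. That removes the contradiction but leaves an ITT population with an exclusion triggered by events after randomisation.

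**Conclusion.** The point holds. IV.5.2 contradicts XII.1 in current text and is at odds with V.5. Applied as written, it excludes patients from the primary non-inferiority analysis because of an emergency or serious adverse event after randomisation.

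The likely numerical effect is unknown and probably small: about 0.04 HbA1c points under the assumed 6% v 2% and 1.0-point deviation, none with equal rates and equal deviations, and in either direction otherwise. The sample size stands. The case for correction rests on the conflicting definition of the primary analysis population, not on a demonstrated large bias.

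**What to change.** Replace the exclusion sentence in IV.5.2 and align the related sections:

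1. Patients whose code is broken stay in the ITT efficacy analysis with every HbA1c value collected, including any from the early-termination visit. Missing week-48 values are handled as for other discontinued patients.
2. They also stay in the safety and hypoglycaemia analyses.
3. The code break is recorded as a protocol deviation. It may exclude the patient from the PPS only, and the PPS definition in XII.1 should say so.
4. A sensitivity analysis repeats the efficacy analyses without these patients. It also covers the symptom-based TCM endpoints, where knowledge of treatment could affect scoring.
5. V.5 and XII.1 use one term, defined once, in place of both ITT and FAS.

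The cost is a short protocol amendment and one additional sensitivity analysis. It needs no extra patients and no new assessments. The missing-data handling that it relies on is needed for discontinued patients in any case.

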**2. Secondary endpoints and indicators**

2.1 Incidence and rate of hypoglycemia;

2.2 General efficacy (FPG, 2hPG, HbAlc) and the efficacy of TCM Syndrome of dual deficiency of *qi* and *yin* ;

2.3 Proportion of patients with HbA1c < 6.5% at 48 week;

2.4 The time to achieve HbA1c <6.5%;

2.4 Changes in islet -cell function (HOMA-IS = 20 × FINS/(FPG-3.5));

2.5 Changes in insulin resistance levels (HOMA-IR = FINS × FPG/22.5);

2.6 Changes in weight, waist circumference, and hip circumference;

2.7 Changes in lipids levels, insulin levels, inflammatory factors (hsCRP), and adiponectin;

2.8 Metabolomics and pharmacogenetics;

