**3. Metabonomics study**

Collect the urine samples of baseline and follow-up at each stage of the trial for testing and analysis of the metabolites. Establish and apply high-throughput, hypersensitized metabolomics detection and analysis technologies, including electron paramagnetic resonance spectrometer, LC and GC-MS as well as automatic biochemical analyzer, combined with laser copolymer fluorescence microscopy and other molecular cytobiology and immunology technologies for testing and analysis of the clinical samples of these populations, in particular the trace and rapid decayed metabolic regulation signaling molecules, metabolites of glibenclamide and the Chinese herbal ingredients in Xiaoke Pills; through qualitative and quantitative analysis, identify the metabolic molecules of specific abnormalities (high or low) to obtain the analysis spectrum of related metabolic molecular, so as to determine the most representative and original corresponding indicators that can accurately reflect the therapeutic response.

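### The A/B code is to stay sealed until all data are analysed and reported, but those data include urinary metabolites of herbs that only the Xiaoke arm receives, so the second-level blind is not protected as ordered

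*Protocol*

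**What the plan says.** Protocol IV.5 sets up two levels of blinding. The first links each case code to group A or B. In the protocol's words, "the second level is that the corresponding treatment of the two groups is either the test group or control group".

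IV.5.3 fixes the order of events. Data are entered, inspected blind and locked. The first unblinding is then to "inform the corresponding group of each case code to biostatistician using the code name A or B for statistical analysis of all data". The names of the arms come last: "When the statistical analysis is ended and the statistical report is completed, the second unblinding is performed". No class of data is excepted.

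Three other places bear on this:

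- III.2 item 2.8 lists "Metabolomics and pharmacogenetics" among the secondary endpoints, and VIII item 9 makes genomic and metabolomic work part of the efficacy evaluation.
- VII.3 gives the sampling: "Collect the urine samples of baseline and follow-up at each stage of the trial for testing and analysis of the metabolites". Among the analytes it names "metabolites of glibenclamide and the Chinese herbal ingredients in Xiaoke Pills".
- VI.1 describes the Xiaoke product ("each pill contains glibenclamide 0.25mg + Chinese herbs") and says that the simulators have no active ingredient.

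**The concern.** The second level of the blind is a single binary label. Anything that shows which code is Xiaoke decodes all 800 patients at once. IV.5.3 asks that this label stay hidden through an analysis whose scope includes an analyte supplied by one arm's treatment. The protocol provides no separate step, later date or separate analyst for that analyte.

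At stake is the reason for having an A/B stage: analytic judgements made after lock should be made without knowing which direction favours the sponsor's product. The protocol leaves some of those judgements open. Section XII allows exploratory analyses as thought fit (item 1), leaves the tests for adverse events to be chosen (item 6), and makes subgroup analyses optional (item 9). A report could therefore be described as blinded to treatment when the label was readable while it was being written.

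**Working it through.** The protocol gives no figure on this point to reproduce. The check is a trace of which arm can supply each analyte, followed by the chance that the label shows.

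**Trace by arm**

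| Data in the metabolomic and genetic work | Xiaoke arm | Glibenclamide arm | Marks the arm? |
|---|---|---|---|
| Glibenclamide metabolites (VII.3) | Yes, from the pill | Yes, from the tablet | Both arms have a source |
| Herbal-ingredient metabolites (VII.3) | Yes, from the pill (VI.1) | No study-drug source, as the simulator has no active ingredient (VI.1) | Yes |
| SNPs from baseline blood (VII.2, IX.2.3) | Fixed before treatment | Fixed before treatment | No |

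VI.7 also bars other Chinese herbs and therapies with a glucose-lowering effect, which limits outside sources of the herbs in the control arm.

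**Order of events under IV.5.3**

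1. Entry, blinded inspection and lock.
2. A/B codes go to the biostatistician for analysis of everything, including secondary endpoint 2.8.
3. The report is completed.
4. A and B are named.

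The herbal-metabolite table belongs to step 2, so the label can be read there, two steps before the code is meant to be opened.

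**Chance that the label shows**

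Inputs:

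- k, Xiaoke patients: the allocation table in IV.6 gives 200 + 200 = 400. With the 20% discontinuation of IV.1, 400 × 0.8 = 320 complete.
- s, the probability that a Xiaoke patient shows a herbal metabolite in at least one post-baseline urine. This is not in the documents, so it is an assumption shown over a range. The trial schedule has 12 post-baseline collections, weeks 4 to 48.
- No detections in the control arm, and independence between patients (assumptions).

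Formula: P(at least one detection) = 1 − (1 − s)^k.

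| s per patient | k = 320 | k = 400 |
|---|---|---|
| 1% | 1 − 0.99^320 = 96.0% | 1 − 0.99^400 = 98.2% |
| 5% | above 99.99% | above 99.99% |
| 20% | above 99.99% | above 99.99% |
| 50% | above 99.99% | above 99.99% |

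The result hardly depends on s. If control urine also showed some positives, one detection would no longer settle the label. The reader would then rely on the difference in rates between A and B, and the calculation above would not apply as it stands.

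**The case against.** The strongest reply is that IV.5.3 fixes when the sealed code is opened, not the order of analyses. HbA1c and safety could be analysed and written up before any metabolite data arrive, or another analyst could handle those data, without breaching the text. XII.1 also defers analysis detail to a separate plan, where data transfer and access rights often sit. The first part stands, and it limits the finding: the blind can be kept. The second does not remove it, because the protocol itself states the unblinding order and its unrestricted scope.

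The harm is also limited. The biostatistician receives the codes only after lock. Symptom scores, hypoglycaemia records and causality ratings are already fixed by then. The primary endpoint is a central-laboratory HbA1c with a stated margin and confidence-interval rule. This stands. A reader might infer that the subjective outcomes are compromised, but a leak after lock cannot alter a recorded value.

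A leak before lock is only conditional. XI.3.1 builds the database from case report form items, and nothing says when urine is assayed or who sees the results.

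A reader might also infer that goal 2.1 ("To discover biomarkers related to the clinical efficacy of Xiaoke Pills with glibenclamide as a reference") and goal 2.3 require the Xiaoke arm to be named before analysis. They do not. Marker effects within A and within B, and marker-by-group interactions, can be fitted on codes and labelled after decoding. Nor do SNP results threaten the blind.

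**Conclusion.** The point holds as a gap in sequencing and access. As ordered, a required secondary analysis can disclose the A/B label before the report is complete, and the protocol contains nothing to prevent it. On the stated assumptions, disclosure has a probability of 96% to 98% even if only 1% of Xiaoke patients are detectable, and is practically certain at 5% or more. The detection rate and the absence of control-arm positives are assumptions, not figures from the protocol.

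The exposure is mainly to analysis choices made after lock. If metabolite results were in hand before lock, a herb-positive urine could also identify individual patients at the blinded inspection. Whether that could happen is not stated.

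The documents do not support the stronger reading that the blind is impossible to keep. It survives if the clinical analyses are reported first or the metabolite data are kept with a separate analyst. The change should be made because it is specific and cheap.

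**What to change.** In IV.5.3, replace *all data* with *all clinical data*. State that the primary, clinical secondary and safety analyses and their report are completed under A/B, and that the second unblinding follows.

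In VII.3, state that herbal-metabolite results stay at the laboratory under sample codes. They should not be released to investigators, data management or the trial biostatistician until that report is final. The alternative is to have a separate analyst handle them and not share results by group before then. SNP results need not be withheld.

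The cost is a few sentences in two sections. Sample size, visits and treatment do not change. The downside is that metabolomic results are reported later than the clinical report.
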